### Study Setting

Participants will be evaluated in person at the key time points outlined in Figure 1 by health care professionals trained in conducting clinical interviews, administering psychological tests, and assessing the ESDC. For patients with SUD, assessments will take place in a designated area within the rehabilitation treatment facility, ensuring both privacy and comfort. Control group participants will be assessed at the University Center of Health Sciences, University of Guadalajara, in Guadalajara, Mexico, by trained health professionals.

Passive monitoring of biological and digital measurements using a smart band will be conducted for at least 22 hours per day, allowing a threshold of 2.4 hours (20%) of lost daily data, 7 days a week. Participants will be required to wear the device during sleep. Participants’ physiological activity will be recorded during various activities and across diverse locations.

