### Digital Measurement of Biomarkers

The Xiaomi Redmi Smart Band 8 will be worn on the user's nondominant hand, positioned 2 cm below the wrist bone and secured at a comfortable level, as instructed by the user manual. The device will be worn for a minimum of 22 hours per day, allowing for an anticipated loss of up to 2 hours of data due to activities such as recharging the device, synchronization with a smartphone, showering, and other routine tasks.

Physiological data, including heart rate (HR), peripheral capillary oxygen saturation, physical activity, stress, and sleep, will be collected using the device's shortest available measurement intervals. Data will capture periods of both high and low activity, during self-reported exercise, regular physical activity, and rest, and will identify any abnormalities in activity patterns.

Data synchronization, which facilitates upload to the associated Xiaomi account, will occur every 72 hours for all participants during the 6- or 18-month study period, as applicable. This data will be downloaded, preprocessed, and stored securely on an encrypted external hard drive and the institution's server for access by authorized research staff within 48 hours (Figures 2A-2E). Participants will receive a reminder notification if synchronization is not completed within 5 days.

Raw data will be used to compute digital the physiological features proposed in a MLM study by Rykov et al, [30] (Table 2).

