**Figure 2 figure2:**
[figure not shown]
Scheme of smart band data retrieval. (A) Data from the smart band Xiaomi Redmi Smart Band 8 via Bluetooth to the smartwatch it’s been linked to for synchronization. (B) Through the Xiaomi app Mi Fitness, the data of the monitored period will be uploaded to the account’s cloud to be downloaded by the researchers. (C) Raw data will be extracted, labeled, and preprocessed. (D) All data will be saved in an assigned encrypted server, property of Universidad de Guadalajara. (E) Alternatively, a second copy will be done on an encrypted external hard drive.

**Table 2 table2:** Summary of raw measurements and physiological features.

	Raw data	Physiological features
Physical activity	Calories, steps, vitality, and time standing up	Daily footsteps, sedentary time, light physical activity, moderate physical activity, and vigorous physical activity
Heart rate (HR)	Beats per minute (BPM), maximum and minimum BPM, and single measure	HR resting HR, daytime HR, nighttime HR, HR delta, and HR root-mean-square successive differences
Sleep	Type of sleep, wake-up time, bedtime, and awake	Coefficient variance, time in bed, total sleeping time, sleep efficiency, sleep onset latency, waking after sleep onset, and sleep midpoint
Rhythm	Activity peaks	Circadian rhythm: COSINOR and nonparametric measurements
Oxygenation	SpO_2_^a^ during daytime, single measures of SpO_2_, and sleep time SpO_2_	—^b^
Stress	Stress level and single stress measurements	—

^a^SpO₂: peripheral capillary oxygen saturation.

^b^Not available.

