### Data Exclusion

Missing data will be addressed through imputation. If more than 20% of daily data samples are missing, they will be excluded. For missing data below this threshold, linear interpolation and neighbor mean imputation (k-nearest neighbor) will be applied during preprocessing using MATLAB.

The quality of data collected from the smart band will be assessed by correlating heart rate at randomly selected timestamps with oxygen saturation, activity levels, self-reported exercise, and sleep type during sleep hours. If atypical correlations are identified, 10 data points before and after the anomaly, along with 5 additional randomly chosen timestamps, will be reviewed. A day with more than 20% of faulty measurements will be excluded from the dataset.

Data will also be excluded in cases of device misuse, such as exchanging the device with other participants or nonparticipants, switching the wearing side without prior notice, or removing the device for more than 5 hours without informing the research team.

If the total sum of missing and excluded data exceeds 20% of the 6-month period, the participant's data will be removed from the study. Finally, for SUD participants, any measurements obtained during periods of substance use will be excluded, and their participation in the study will be terminated.

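### Study Setting labels 2.4 hours of lost daily data as 20%, but 2.4 hours is about 10% of a day; the 20% that excludes data elsewhere is about twice as large

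*Protocol article*

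**What the plan says.** Four statements in the protocol article bear on how much daily data may be lost.

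- **Study Setting:** monitoring is to run for "at least 22 hours per day, allowing a threshold of 2.4 hours (20%) of lost daily data".
- **Digital Measurement of Biomarkers:** the band is worn for a "minimum of 22 hours per day, allowing for an anticipated loss of up to 2 hours of data", to cover charging, synchronization, showering and similar tasks. No consequence is attached to falling short.
- **Data Exclusion, daily level:** "If more than 20% of daily data samples are missing, they will be excluded". A parallel rule covers quality: "A day with more than 20% of faulty measurements will be excluded from the dataset". Smaller amounts of missing data are imputed. The section also excludes data when the band is off for more than 5 hours without notice.
- **Data Exclusion, participant level:** "If the total sum of missing and excluded data exceeds 20% of the 6-month period, the participant's data will be removed from the study". Withdrawal Criteria has a similar 20% limit for non-use or misuse over the six months.

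**The concern.** Study Setting gives one tolerance in two units, and the units disagree by a factor of about two. That would be a slip of little weight if the figure were only descriptive. But 20% is also the figure that Data Exclusion uses to decide which days enter the data set. Excluded days then count towards a second 20% limit that removes the participant. Someone coding the filter in hours could take 2.4 h from Study Setting; someone coding it as a fraction would take 20% from Data Exclusion. The two data sets can contain different days and different people.

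The groups are small: the minimum is 25 each, and 18 patients with SUD and 17 controls had been enrolled by June 2025. One participant removed from a group of 25 is 1/25 = 4% of it. The Results section says device data are already at the labeling and preprocessing stage, which is where these limits apply.

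**Working it through.** **Inputs.** 2.4 h, 20% and 22 h (Study Setting); 22 h and 2 h (Digital Measurement of Biomarkers); 20% of daily samples, 20% of six months and 5 h (Data Exclusion). Assumptions: six months is 183 days, and samples are spread evenly over the day, so that a share of samples can be read as a share of hours.

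**1. Can 2.4 h = 20% be reproduced?**

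| Base | 2.4 h as a share | 20% in hours | 2 h as a share |
|---|---|---|---|
| 24 h (full day) | 2.4/24 = 10.0% | 0.20 × 24 = 4.8 h | 2/24 = 8.3% |
| 22 h (required wear) | 2.4/22 = 10.9% | 0.20 × 22 = 4.4 h | 2/22 = 9.1% |
| 12 h | 2.4/12 = 20.0% | 0.20 × 12 = 2.4 h | 2/12 = 16.7% |

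The stated equality holds only on a 12-h base, which the document uses nowhere.

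**2. Is the sentence consistent with its own minimum?** 24 − 2.4 = 21.6 h, which is below 22 h. A 22-h minimum leaves 24 − 22 = 2 h, which is the figure in Digital Measurement of Biomarkers.

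**3. Effect on a single day**, if each figure were applied as the exclusion limit:

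| Hours lost | Limit 2.4 h | Limit 4.4 h (20% of 22 h) | Limit 4.8 h (20% of 24 h) |
|---|---|---|---|
| 2.2 | kept | kept | kept |
| 3.0 | excluded | kept | kept |
| 4.5 | excluded | excluded | kept |
| 4.9 | excluded | excluded | excluded |

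Days with losses between 2.4 h and 4.8 h (or 4.4 h) are the ones in dispute.

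**4. Effect on a participant.** The removal limit is 0.20 × 183 = 36.6 days, so 37 fully excluded days exceed it. Take a participant who loses 3 h (3/24 = 12.5%) on 37 days and nothing on the others.

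- Limit 2.4 h: 37 days excluded, 37/183 = 20.2%, above 20%. Participant removed.
- Limit 4.8 h: no day excluded. Missing data are 37 × 3/24 = 4.6 days, and 4.6/183 = 2.5%. Participant kept.

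If the same 3 h were lost every day, all days would be excluded at 2.4 h and the participant removed. At 4.8 h the total loss would be 12.5% and the participant kept.

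**5. The 5-h rule.** 5/24 = 20.8%, close to but not equal to 20% of 24 h. It is a further daily limit and depends on whether notice was given.

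**The case against.** The strongest reply is that only Data Exclusion states a consequence for the amount of data missing, and its threshold is 20%. Study Setting carries the same 20% label and excludes nothing, so a careful programmer would follow Data Exclusion and the 2.4 h would do no harm. The first part stands: the difference in who is analysed arises only if 2.4 h is coded as the limit. But the sentence calls 2.4 h a threshold for lost daily data and equates it with the percentage that triggers exclusion, so that coding is a foreseeable reading.

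It can also be said that the 2.4 h might be a tolerance below the 22-h target, on top of the 2 h already expected. Then 2 + 2.4 = 4.4 h, which is 20% of 22 h. This is possible, but the text does not say it. The label is attached to 2.4 h itself, and Data Exclusion names no 22-h base. It does show that the intended figure cannot be settled from the document.

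Two stronger readings are tempting and are not supported.

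- A reader might infer that a day with less than 22 h of wear is deleted. No section says so. The 22 h and 2 h are a wear requirement and an expected loss, with no stated consequence.
- A reader might infer that filling gaps by linear interpolation shrinks variability features such as "HR root-mean-square successive differences" (Table 2). Digital Measurement of Biomarkers says the features are computed from raw data, no section places that step after imputation, and a nearest-neighbor method is named as well. No size can be put on such an effect from this document.

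That less adherent participants differ in relapse risk is plausible, but the document gives no data on it, and the point does not depend on it.

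**Conclusion.** The point holds as an arithmetic error and an internal inconsistency in a data-validity threshold. The equality in Study Setting is wrong on both bases that the document offers, and the 2.4 h also breaches the minimum in its own sentence. The same 20% label therefore covers limits that differ twofold on a 24-h base (4.8/2.4 = 2) and 1.8-fold on a 22-h base (4.4/2.4).

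The consequence is conditional: if 2.4 h is applied as the daily limit, 37 days with 3 h lost are enough to remove a participant whom the 20% rule keeps with 2.5% missing. That example is constructed, and how many participants it would affect is unknown. It rests on a 183-day period and even sampling; Data Exclusion counts samples, so 4.8 h is derived and not printed. The correction should be made before the exclusion rules are coded.

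**What to change.** Correct Study Setting so that its hours and percentage agree with each other and with Data Exclusion, and state one daily validity limit with its base (24 h or 22 h, hours or samples). The sponsor must confirm which figure was meant. If the operative 20% rule of Data Exclusion is kept on a 24-h base, the limit is 4.8 h lost (19.2 h of data) under even sampling, and the 2.4-h figure is deleted.

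Label the 22-h minimum and the 2-h expected loss, in both sections where they occur, as the wear instruction only, with no bearing on exclusion. Check the chosen limit against the 5-h removal rule, and say which governs when a removal longer than 5 h was announced in advance.

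The cost is a few lines of text. The downside of adopting 4.8 h over 2.4 h is that some days with longer gaps are retained, and more of their data are imputed.

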### Data Collection, Storage, and Protection

Digital measurements will be downloaded from a Xiaomi account as a password-protected zip file. The csv files containing data from the linked devices will be processed and coded before being securely stored for future use. Clinical data will be entered into the database under a unique study ID number, either directly from source materials or from the instruments used for assessment.

In compliance with ISO (International Organization for Standardization)/IEC (International Electrotechnical Commission) 29100 guidelines and the General Data Protection Regulation (GDPR) [66,67], all data will be stored in encrypted storage units housed within the Department of Neuroscience at CUCS, University of Guadalajara. In addition, all files will be backed up on an encrypted cloud system hosted by the University of Guadalajara servers. During the study, access to these databases will be restricted to authorized study staff with the necessary training and permissions, ensuring the privacy and confidentiality of participants.

### Instruments

The study instruments that will be used in this protocol to measure each assessment category referred to in the timeline (Figure 1), are presented in Table 1.

**Table 1 table1:** Study instruments.

Instrument	Period				
	Baseline	3 Months	6 Months	18 Months	Continuous
Wearable: Xiaomi Redmi Smart Band 8^a^	✓	✓	✓	✓ ^b^	✓
Demographic survey^c^	✓				
The Adverse Childhood Experiences Assessment (ACEs)^d^	✓				
The University of Rhode Island Change Assessment Scale (URICA)^d^	✓				
The Alcohol, Smoking and Substance Involvement Screening Test (ASSIST)^d^	✓				
The Beck Depression Inventory (BDI-II)^d^	✓				
The Beck Anxiety Inventory (BAI-II)^d^	✓				
The Pittsburgh Sleep Quality Index (PSQI)^d^	✓		✓	✓^b^	
Wechsler Adult Intelligence Scale IV (WAIS-IV): Digit Span and Letter-Number Sequencing subscales^d^	✓		✓		
Emotional Pictures Database (EmoMadrid)^e^		✓	✓		
Mannheimer Craving Scale (MaCS)^e^	✓	✓	✓		
Automatic facial emotion recognition software (FER)^e^		✓	✓		

^a^Digital measurement of biomarkers.

^b^Substance use disorder group only.

^c^Demographic assessment.

^d^Psychological assessments.

^e^Emotional state during craving assessment.

### Digital Measurement of Biomarkers

The Xiaomi Redmi Smart Band 8 will be worn on the user's nondominant hand, positioned 2 cm below the wrist bone and secured at a comfortable level, as instructed by the user manual. The device will be worn for a minimum of 22 hours per day, allowing for an anticipated loss of up to 2 hours of data due to activities such as recharging the device, synchronization with a smartphone, showering, and other routine tasks.

Physiological data, including heart rate (HR), peripheral capillary oxygen saturation, physical activity, stress, and sleep, will be collected using the device's shortest available measurement intervals. Data will capture periods of both high and low activity, during self-reported exercise, regular physical activity, and rest, and will identify any abnormalities in activity patterns.

Data synchronization, which facilitates upload to the associated Xiaomi account, will occur every 72 hours for all participants during the 6- or 18-month study period, as applicable. This data will be downloaded, preprocessed, and stored securely on an encrypted external hard drive and the institution's server for access by authorized research staff within 48 hours (Figures 2A-2E). Participants will receive a reminder notification if synchronization is not completed within 5 days.

Raw data will be used to compute digital the physiological features proposed in a MLM study by Rykov et al, [30] (Table 2).

**Figure 2 figure2:**
[figure not shown]
Scheme of smart band data retrieval. (A) Data from the smart band Xiaomi Redmi Smart Band 8 via Bluetooth to the smartwatch it’s been linked to for synchronization. (B) Through the Xiaomi app Mi Fitness, the data of the monitored period will be uploaded to the account’s cloud to be downloaded by the researchers. (C) Raw data will be extracted, labeled, and preprocessed. (D) All data will be saved in an assigned encrypted server, property of Universidad de Guadalajara. (E) Alternatively, a second copy will be done on an encrypted external hard drive.

**Table 2 table2:** Summary of raw measurements and physiological features.

	Raw data	Physiological features
Physical activity	Calories, steps, vitality, and time standing up	Daily footsteps, sedentary time, light physical activity, moderate physical activity, and vigorous physical activity
Heart rate (HR)	Beats per minute (BPM), maximum and minimum BPM, and single measure	HR resting HR, daytime HR, nighttime HR, HR delta, and HR root-mean-square successive differences
Sleep	Type of sleep, wake-up time, bedtime, and awake	Coefficient variance, time in bed, total sleeping time, sleep efficiency, sleep onset latency, waking after sleep onset, and sleep midpoint
Rhythm	Activity peaks	Circadian rhythm: COSINOR and nonparametric measurements
Oxygenation	SpO_2_^a^ during daytime, single measures of SpO_2_, and sleep time SpO_2_	—^b^
Stress	Stress level and single stress measurements	—

^a^SpO₂: peripheral capillary oxygen saturation.

^b^Not available.

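### Daily step totals have no worn-time denominator and gaps in counts may be interpolated, so wear time can pass into the activity features as apparent physical activity

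*Protocol article*

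**What the plan says.** Table 2 gives the raw physical-activity inputs as "Calories, steps, vitality, and time standing up" and the derived features as "Daily footsteps, sedentary time, light physical activity, moderate physical activity, and vigorous physical activity". Only footsteps carry a time unit. Neither list contains an off-wrist flag or hours worn.

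Three places state how much daily loss is acceptable:

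- Digital Measurement of Biomarkers asks for at least 22 h of wear, "allowing for an anticipated loss of up to 2 hours of data due to activities such as recharging the device" and other routine tasks.
- Study Setting asks for "at least 22 hours per day, allowing a threshold of 2.4 hours (20%) of lost daily data, 7 days a week".
- Data Exclusion says "If more than 20% of daily data samples are missing, they will be excluded".

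On days that are kept, the rule is: "For missing data below this threshold, linear interpolation and neighbor mean imputation (k-nearest neighbor) will be applied during preprocessing using MATLAB". It makes no distinction between continuous signals, such as heart rate, and counts, such as steps.

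The features feed a model that separates healthy men from patients with SUD and also predicts therapy duration and relapse latency (Predictive Model; Output). Facility staff synchronise the patients' bands with a community phone (Recruitment), while controls synchronise and upload their own data (Control Participants).

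**The concern.** A daily total reflects both behaviour and the hours observed. Off-wrist time can alter it in two ways. If the band records zero steps while off and those minutes are not recognised as missing, the total falls. If the minutes are recognised as missing, the stated rule fills them, and for a count this inserts steps nobody observed. Interpolation is reasonable for a slowly varying signal, but a step count is bursty and often zero, so the readings on either side of a gap say little about what happened within it.

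What is at stake is the meaning of the activity features. The two groups wear the band under different conditions, and among patients the time worn may follow engagement with treatment. If wear does differ, the SUD digital phenotype and the relapse model could pick up wear under the name of activity. The planned clustering by time of day and reported activity (Limitations and Considerations) does not address this.

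**Working it through.** **1. The plan's own loss limits.**

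- Data Exclusion: 0.20 × 24 h = 4.8 h.
- Study Setting: 2.4 h / 24 h = 10%, not 20%. The figure of 2.4 h is 20% only of a 12 h base (2.4 / 12 = 0.20), which the article does not state.
- Digital Measurement of Biomarkers: 24 − 22 = 2 h, and 2 / 24 = 8.3%.

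The stated equivalence of 2.4 h and 20% does not reproduce on a 24 h day, and the three limits differ. The separate rule against "removing the device for more than 5 hours without informing the research team" does not tighten them: 5 h is longer than 4.8 h, and the rule covers only unannounced removal.

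**2. If off-wrist time is logged as zero.** Assumptions, not in the article: 16 waking hours, 500 steps per waking hour (16 × 500 = 8,000 a day), and all off-wrist time while awake.

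Daily total = 500 × (16 − hours off). Relative error = −(hours off) / 16.

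| Hours off | Daily total | Error | Steps per worn waking hour |
|---|---|---|---|
| 0 | 8,000 | 0% | 500 |
| 2 | 7,000 | −12.5% | 500 |
| 2.4 | 6,800 | −15% | 500 |
| 4.8 | 5,600 | −30% | 500 |

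With 15 to 17 waking hours, the 2 h error is 11.8% to 13.3% and the 4.8 h error 28% to 32%. The rate per worn hour does not move.

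**3. If the gap is filled.** Inserted steps = hours off × mean rate of the bracketing readings. True steps in the gap = hours off × 500. The bracketing rates are assumed.

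| Gap | Bracketing rate 100/h | 500/h | 1,500/h | True |
|---|---|---|---|---|
| 2 h | 200 | 1,000 | 3,000 | 1,000 |
| 4.8 h | 480 | 2,400 | 7,200 | 2,400 |

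For the 2 h gap the day's total becomes 7,000 + 200 = 7,200 (−10%) or 7,000 + 3,000 = 10,000 (+25%). The error can go either way, depending on when the band comes off.

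**4. What a wear difference between groups would do.** Take the zero-logging route, no true difference in activity, and an assumed between-person SD of 1,500 to 3,000 steps. A wear difference of h hours shifts mean steps by 500 × h, so d = 500h / SD and the single-feature AUC = Φ(d / √2).

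| Wear difference | Shift in steps | AUC (SD 3,000 to 1,500) |
|---|---|---|
| 0 h | 0 | 0.50 |
| 1 h | 500 | 0.55 to 0.59 |
| 2 h | 1,000 | 0.59 to 0.68 |
| 4.8 h | 2,400 | 0.71 to 0.87 |

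If both groups keep to 22 h of wear, the largest possible difference is 2 h, and that needs one group at no loss and the other at the limit. The 4.8 h row is the extreme the 20% rule permits, not an expected case.

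**The case against.** Table 2 is a summary. The article says the features follow a cited study, and units or valid-minute rules are commonly left to a fuller document. That stands for the four features without a unit: they may already be shares of worn time, and it would be wrong to say that all five are daily amounts. It does not cover the daily label on footsteps or the interpolation rule, both of which are stated.

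The plan also has safeguards: the same 22 h target for everyone, a check of heart rate against activity at sampled timestamps, exclusion of days with more than 20% faulty measurements, and a 20% cap per participant over six months. These limit the problem. None of them sets a wear rule for the activity features or removes the dependence on wear within kept days.

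Two stronger readings are tempting. One is that off-wrist hours are counted as inactivity. The article does not say what the band records when it is off, and for gaps recognised as missing its written rule is imputation. The other is that wear time will be read as a sign of SUD. That needs wear to differ between the groups, and the article neither reports such a difference nor implies its direction; with equal wear the AUC stays at 0.50. A reader might also compute false-positive rates for sedentary time. With 25 per group, a 1 h/day wear difference and an assumed SD of 1.5 to 2.5 h, a two-sample t-test rejects in 28% to 64% of studies. That arithmetic is right, but it rests on a feature whose unit is not given, on zero-logging, and on a large wear gap under the 22 h target.

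Finally, if wear follows engagement it may be a legitimate predictor of relapse. That is fair, but it should then enter the model under its own name and not inside the step count.

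**Conclusion.** The point holds as a limited fault in the plan. Under the stated rules the daily step total depends on hours worn, and count gaps on kept days are filled by a method that does not suit them. At the plan's own anticipated loss of 2 h, the error is about −12.5% if zeros are logged (16 waking hours assumed), or of either sign if the gap is filled. Whether this distorts the SUD-control comparison or the relapse model depends on differential wear, which is possible given the different conditions of use but is not documented. It is a risk to remove, not a demonstrated bias. The step rates, waking hours and SDs used here are assumptions. The conflict between 2 h, 2.4 h and 20% of the day comes directly from the text.

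**What to change.** - Define wear from heart-rate availability at the device's sampling interval, and leave unworn minutes out of all activity features.
- In Table 2, express steps and light, moderate and vigorous activity per worn waking hour, and sedentary time as a share of worn waking time.
- In Data Exclusion, exempt step and activity counts from interpolation and nearest-neighbour filling.
- Report worn hours per day by group, and adjust the SUD-control activity comparisons for them.
- Reconcile the three limits on daily data loss so that hours and percentage agree on one stated base.

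The cost is a small change to the feature script and to the text. Heart rate is already collected, and the data in hand are still at the labelling and preprocessing stage (Results), so the change can be made now. The features will rest on slightly fewer minutes per day. A rate per worn hour also assumes that unworn waking time resembles worn time, which is why worn hours should be reported as well.
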